# The effects of antifungal therapy on the recurrence of aspergillus infection after pulmonary aspergilloma resection: a study protocol for a single-center, prospective, non-blind, randomized, 24-month, parallel group study

**DOI:** 10.1186/s12890-021-01702-4

**Published:** 2021-10-29

**Keywords:** Antifungal therapy, Aspergilloma, Safety, Recurrence

## Abstract

**Background:**

In recent years, the incidence of pulmonary aspergilloma has increased. The harm of aspergilloma is life-threatening massive hemoptysis, and the conventional treatment is surgical treatment. However, whether the antifungal treatment after surgery is required and the course of treatment before and after surgery are still unclear.

**Methods:**

In this study, patients with pulmonary aspergilloma confirmed pathologically after surgery will be selected as subjects to conduct a single-center, randomized, parallel grouping, prospective, 2-year clinical study. Through regular visits, the recurrence of aspergillus infection, quality of life, lung function indicators, safety of antifungal therapy and other indicators were recorded to evaluate the recurrence risk of aspergillus infection and safety of antifungal agents. Cox proportional risk regression model was used to analyze the influencing factors of antifungal therapy on aspergillus infection recurrence after aspergillus bulbectomy. Cox multiple regression model was used for optimal model fitting, and regression coefficient (β), relative risk (RR) and 95% confidence interval of RR were calculated.

**Discussion:**

The study will explore whether antifungal therapy could improve the quality of life, reduce the recurrence of aspergillus infection, and ultimately improve the prognosis of patients with aspergilloma. The study results will provide high-quality evidence-based medical evidence for the formulation, revision and optimization of international and domestic clinical guidelines and expert consensus on chronic aspergillus lung disease, effectively improve the clinical treatment effect of aspergilloma, and form the latest concept of diagnosis and treatment of aspergilloma.

*Trial registration*: The trial was registered on the Chinese Clinical Trial Registry website (https://www.chictr.org.cn/showprojen.aspx?proj=33231). Registration number: ChiCTR1800019990.

## Background

Pulmonary aspergilloma is a kind of aspergillus parasitic in the lung cavity, mycelium and cell debris inside the hole to form a sphere. It most commonly occurs in the existing pulmonary cavity, including tuberculosis, lung abscess, bronchiectasis, pulmonary cyst, cytoplasmic disease, lung cancer and other diseases of pulmonary cavity formation, which is one of the lung intractable infectious diseases. The harm of aspergilloma is life-threatening massive hemoptysis. Currently, there is no consensus on the best treatment of aspergilloma, and there is a lack of double-blind, randomized, placebo-controlled clinical studies on its treatment. Information on treatment comes mainly from case reports and retrospective studies. In general, patients with asymptomatic aspergilloma do not need special treatment and can be observed regularly [1], and treatment is only considered when patients have symptoms of hemoptysis [2]. Some scholars believe that surgery is the best treatment [3, 4]. As for the acute and long-term prognosis of patients with pulmonary aspergilloma treated by surgery, studies [5] showed that the overall survival rate at 2, 5 and 10 years was 86.6%, 79.4% and 79.4%, respectively, and the disease-free survival rates were 86.6%, 72.6% and 72.6%, respectively. The survival rate may be affected by the absence of antifungal treatment, postoperative pulmonary dysfunction and recurrence of fungal infection. These questions need to be further explored in clinical studies. This study was designed to evaluate the difference in recurrence risk of aspergillus infection and safety of antifungal agents in patients with pathologically confirmed aspergilloma after surgery in a single-center, randomized, parallel grouping, prospective, 2-year clinical study.

## Methods

### Study design and setting

The study was a single-center, prospective, non-blind, randomized, 24-month parallel controlled trial. The data of patients diagnosed with aspergilloma and surgically excision from Shanghai Pulmonary Hospital from January 1, 2020 to December 31, 2022 will be collected. After providing informed consent, enrolled patients will be randomly assigned for study group or the control group at a ratio of 1:1 using the block randomization method. Each patient will then receive a numeric randomization code. According to the literature and the results of the preliminary experiment, the recurrence rate of the experimental group is expected to be less than 1%, and that of the control group is about 20%. According to the ɑ value of 0.05 and the degree of certainty of 0.8, the sample content of each group is estimated by PASS 15 software to be 37 people, with the amplification of 1.1 times, and 40 patients are planned to be included in each group.

The study group will receive voriconazole orally for three months, twice a day, 0.2 g each time. The control group will not receive antifungal therapy. Detailed research process is described in Fig. 1.

**Fig. 1 Fig1:**
[figure not shown]
Research process and flow chart

### Inclusion criteria

All the following criteria must be met: (1) Aspergillomas are in the lung. (2) Patients with clear pathological diagnosis of aspergilloma and surgical resection. (3) Written informed consent is signed.

### Exclusion criteria

(1) Patients with a severe disease other than the lung that, in the investigator’s judgment, would put the subject at risk for participating in the study or affect the results of the study and the subject’s ability to participate in the study. (2) Patients with a history of serious heart disease, such as acute myocardial infarction, congestive heart failure (NYHA cardiac function grade III and above), severe arrhythmia and other acute heart disease. (3) Serious primary diseases of important organs and systems, such as acute stroke, moderate or above hypertension after treatment, active gastric ulcer, diabetes (with serious complications), malignant tumor, etc. (4) Patients with confirmed and suspected lung cancer. (5) Limited understanding ability and poor compliance. (6) No legal capacity or limited legal capacity. (7) Those who participated in clinical trials of other drugs within 30 days before screening and did not reach the end point. (8) Pregnant and lactating women and women of childbearing age who do not agree to use effective contraceptive measures during the study. (9) Persons with mental or physical disabilities. (10) Suspected or true history of alcohol and drug abuse. (11) Known intolerance to drug treatment. (12) Aspartate aminotransferase (AST) and Alanine transaminase (ALT) three times higher than the upper limit of normal, creatinine more than 176.8 mmol/L. (13) Shock or other hemodynamic instability. (14) Those who are in the active stage of infectious diseases such as hepatitis A, hepatitis B, Acquired Immune Deficiency Syndrome (AIDS), tuberculosis and connective tissue diseases. (15) The researcher considers it inappropriate to participate in this study.

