### Safety indicators

Including recurrence of aspergillus infection and adverse reactions such as liver and kidney function damage and etc.

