In general, more evidence-based medical evidence is needed to explore whether antifungal agents should be used after aspergilloma surgery, the appropriate course of treatment and the safety of drugs. There are both advantages and disadvantages of antifungal therapy. The disadvantages are the high expense of antifungal drugs, the heavy economic burden on patients, and the high risk of liver and kidney function damage caused by antifungal drugs. The advantage of antifungal therapy is that it may reduce the risk of aspergillus recurrence. The advantage of non-antifungal therapy is to reduce the overtreatment in some cases and reduce the economic burden of patients. But its disadvantage is that the risk of fungal infection recurrence may be increased. Therefore, more clinical studies are needed to provide evidence-based medical evidence for the following issues: (1) Further analysis is needed to determine whether anti-fungal treatment after aspergilloma bulbectomy has an impact on recurrence of aspergillus infection. (2) Duration and safety of antifungal therapy.

This study was designed to evaluate the difference in recurrence risk and safety of antifungal agents in patients with pathologically confirmed aspergilloma after surgery in a single-center, randomized, parallel grouping, prospective, 2-year clinical study. Through regular supervision record of aspergilloma recurrence, the quality of life, lung function and safety evaluation of fungi treatment, to explore the most suitable treatment for aspergilloma, to improve the quality of life of patients with more advantages, reduce the recurrence of aspergillus infection, improve the prognosis of patients with aspergilloma eventually. The study results will provide high-quality evidence-based medical evidence for the formulation, revision and optimization of international and domestic clinical guidelines and expert consensus on chronic aspergillus lung disease, effectively improve the clinical treatment effect, and form the latest concept of diagnosis and treatment of aspergilloma.

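### The creatinine limb of exclusion criterion 12 is printed in a unit that makes it unreachable, leaving the article without a working numeric renal threshold

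*Protocol article*

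**What the plan says.** Criterion 12 in the protocol article's Exclusion criteria has two laboratory limbs. The first concerns liver enzymes: "Aspartate aminotransferase (AST) and Alanine transaminase (ALT) three times higher than the upper limit of normal". The second concerns renal function: "creatinine more than 176.8 mmol/L". This is the only creatinine value, and the only creatinine unit, in the article.

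Other exclusion criteria could touch renal disease without giving a number:

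- Criterion 1 covers severe disease outside the lung that the investigator judges to be a risk.
- Criterion 3 covers "Serious primary diseases of important organs and systems", with an open-ended list of examples that does not name the kidney.
- Criterion 15 is fully discretionary: "The researcher considers it inappropriate to participate in this study".

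The section on safety indicators lists "adverse reactions such as liver and kidney function damage". The Discussion counts among the drawbacks of treatment "the high risk of liver and kidney function damage caused by antifungal drugs". Table 1 schedules a blood biochemical test at screening, and the section on clinical data to be collected includes kidney function among the biochemical indexes. Trial status reports that recruitment is open, with 8 patients enrolled at the time of writing; Study design and setting plans 40 per group.

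**The concern.** An eligibility limit works only if some patients could exceed it. At the printed unit, the creatinine limit lies far above anything a blood sample could show, so it separates no one from anyone else. If the operative documents carry the same text, a patient with markedly raised creatinine breaches no numeric criterion at screening.

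Two things are at stake. First, this is the article's only objective renal limit, in a trial that gives one arm three months of an antifungal drug and records kidney damage as a safety outcome. Second, the Elimination criteria make a breach of the inclusion or exclusion criteria a ground for considering a subject's removal before the analysis. With an impossible limit, a patient with renal impairment either breaches nothing in writing or is judged against an unwritten reading of the unit. In a non-blind trial that reading should be settled on paper before anyone's eligibility is questioned.

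**Working it through.** **Inputs**

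- Printed threshold: 176.8 mmol/L (Exclusion criteria, item 12).
- Molar mass of creatinine, C4H7N3O. This is a chemical constant that the article does not give. From atomic masses: 4 × 12.011 + 7 × 1.008 + 3 × 14.007 + 15.999 = 113.12 g/mol.

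The threshold is a stated constant. The article gives nothing from which it could be derived, so there is no figure of the plan's own to reproduce, and the check is a unit conversion.

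**Step 1. The threshold as printed**

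Mass concentration = molar concentration × molar mass.

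176.8 mmol/L = 0.1768 mol/L, and 0.1768 × 113.12 = 20.0 g/L.

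20.0 g/L × 100 (1 g/L = 100 mg/dL) = about 2,000 mg/dL.

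**Step 2. The same numeral in micromol/L**

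176.8 × 10⁻⁶ mol/L × 113.12 g/mol = 0.0200 g/L, and 0.0200 × 100 = 2.00 mg/dL.

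Cross-check by the conversion factor: 1 mg/dL = 10 mg/L, and 10 / 113.12 = 0.0884 mmol/L = 88.4 micromol/L, so 176.8 / 88.4 = 2.0.

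**Step 3. Size of the discrepancy**

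2,000 / 2.00 = 1,000, exactly the step from milli to micro. A numeral with four significant figures that becomes a round 2.0 mg/dL under one change of prefix points to a slip in the prefix, not in the digits.

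**Step 4. Could the text conversion have lost a micro sign?**

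The unit reads as milli, not as a gap or a stray symbol. Greek-type characters survive elsewhere in the same text: the alpha in the sample-size paragraph, and the beta in the glucan assay name and in the regression coefficient. A conversion artefact cannot be ruled out completely, but nothing in the text points to one.

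**Step 5. What still operates**

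| Criterion | Works as written? | Numeric renal limit? |
|---|---|---|
| 12, AST/ALT limb | Yes | No |
| 12, creatinine limb | No | Printed, but unreachable |
| 1, severe disease outside the lung | Yes, by judgement | No |
| 3, serious organ disease | Yes, kidney not named | No |
| 15, researcher's opinion | Yes, by judgement | No |

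The creatinine limb excludes 0% of patients as printed. The other rows can still exclude patients, but none supplies a renal number.

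**The case against.** The strongest reply is that the practical effect is probably small. The printed value is so implausible that screening staff would be expected to notice it and read it as micromol/L. Kidney function is measured, biochemistry is done at screening, and three other criteria let the investigator turn away a patient with serious renal disease. The article condenses a protocol that is not shown, and the working protocol, laboratory form or case report form may carry another unit. No passage shows that any patient was screened against the literal value. All of this stands, and it limits the seriousness of the point. It does not make the printed figure right, and discretionary criteria do not replace a stated limit.

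A reader might infer three stronger things that the article does not support.

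- *That criterion 12 as a whole is void.* It is not; the AST/ALT limb is unaffected by the unit.
- *That the error confounds the kidney-safety comparison.* Eligibility is settled before 1:1 block randomization, so a void limit changes who enters both arms alike. It could add noise or chance imbalance in arms of about 40, but not systematic bias between them.
- *That the article warns of kidney damage from the study drug by name.* The Discussion speaks of antifungal drugs as a class. The firmer support is the listing of kidney damage as a safety indicator.

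**Conclusion.** The point holds for the creatinine limb of criterion 12. As printed, the limit is about 2,000 mg/dL, which is 1,000 times what the same numeral gives in micromol/L. This limb therefore excludes nobody, and the article has no working numeric renal threshold.

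The conclusion rests on three assumptions: the molar mass of 113.12 g/mol; the general knowledge that 20 g of creatinine per litre is unattainable; and reading the two limbs of criterion 12 as alternatives, since only a comma joins them. That the intended unit was micromol/L is a strong inference from the arithmetic, not something the article states. Whether the limit is clinically suitable in any unit is outside this review.

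The sample size, randomization, primary endpoint and planned regression are untouched. The error concerns an eligibility figure that is meant to be applied, so it is more than a background misprint. It is a should-fix correction, and the article gives no evidence that an unsuitable patient was enrolled.

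**What to change.** Compare the unit in criterion 12 with the full protocol, the screening form or case report form, and the laboratory's reporting unit. Settle one threshold with clinical sign-off and print it identically in all of them. If only the article is wrong, a published correction of the unit is enough.

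If the operative documents carry the same unit, also check the screening creatinine of every patient already enrolled against the confirmed threshold, and record the outcome before any decision on eliminating subjects from the analysis.

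The cost is one word in the text and a check of records that should already exist, because biochemistry is scheduled at screening. That was 8 records when the article was written. With 2 × 40 = 80 patients planned, a correction at that time would have come before the other 80 − 8 = 72 were enrolled.

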### Exit criteria

Withdrawal decided by the researcher:(a) Refers to the decision of the investigator to withdraw an enrolled subject from the study if it is not suitable to continue the study during the study. (b) Subjects have poor compliance with the protocol. (c) Severe adverse events or intolerable adverse events occur during the study. (d) The subject has some comorbidities, complications or special physiological changes and is not suitable for further study. (e) Other circumstances in which the investigator determines the need to withdraw from the study.Subjects voluntarily withdraw from the study:(a) The subject is unwilling to continue the clinical trial and proposes withdrawal to the investigator. (b) lost to follow-up. (c) Subjects who withdraw early shall indicate the reasons for withdrawal on the case report form. Patients who withdraw due to adverse events should be followed up until the adverse events disappear or have a clear explanation.

### Elimination criteria

Prior to statistical analysis of the data, the main researcher, the sponsor and the statistical unit shall judge whether to exclude the individual cases. If one of the following situations occurs, the principal investigator shall comprehensively judge whether to exclude the subject based on the degree of completion of the test and the reasons for withdrawal, and make relevant explanations:

The selection of individual subjects violates the inclusion/exclusion criteria and should not be included in the test;During the study period, the researcher considers that the subject has other factors that can not continue to participate in the study, and actually discontinues the subject’s continued participation in the study;During the test, the subjects do not comply with the test plan and the compliance is poor. For example, the samples for effectiveness and safety evaluation cannot be collected as required by the test plan, and there is no data, etc.The Investigator has the right to discontinue the subject’s participation in the study if: the investigator must carefully evaluate the discontinued subject, take active treatment, and record this procedure in detail in the original notebook. If a subject withdraws from the study due to an adverse event, abnormal laboratory test values, or test failure, he or she must also be assessed and treated accordingly, and this procedure must be documented in detail in the original notebook. The investigator may also determine at any time during the study whether or not the subject should continue the clinical trial based on medical judgment.Termination test standard:Termination of a trial is when the trial has not completed the evaluation of all subjects as planned. After cessation of the study, new subjects will not be included, and those enrolled but not yet out of the study will be examined and interviewed in accordance with the investigator’s consultation. If the study is found to have no clinical value during the trial, the trial should be terminated;(a) Major errors in the clinical trial protocol were found during the trial, making it difficult to evaluate the effect of the study. (b) If serious deviations occur in the implementation of the test, the test should be stopped if it is difficult to evaluate the effect of the study if it continues. (c) Termination at the request of the investigator (for reasons of funding, management, etc.). (d) The China Food and Drug Administration orders the termination of the trial for some reason. (e) The ethics committee shall terminate the trial from the perspective of protecting the rights and interests of the subjects.

For all subjects who terminate the study early, the investigator should obtain, as far as possible, the reason for withdrawal from the study, such as adverse events, ineffectiveness of corrective actions, withdrawal based on the investigator’s decision, or other reasons, and the reason for withdrawal should be recorded in the case report form (CRF). Subjects who quit early should complete the early exit interview according to the schedule of the visit procedure.

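### Randomised patients may be excluded before analysis by unblinded, case-by-case judgement on post-randomisation grounds, so the primary comparison is not protected and a spurious voriconazole benefit is possible

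*Protocol article*

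**What the plan says.** Under Study design and setting, the protocol article states: "The study was a single-center, prospective, non-blind, randomized, 24-month parallel controlled trial". Patients are "randomly assigned for study group or the control group at a ratio of 1:1 using the block randomization method". One arm takes oral voriconazole; for the other, "The control group will not receive antifungal therapy".

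The Elimination criteria section then sets a step between data collection and analysis. Its opening sentence gives the main researcher, the sponsor and the statistical unit the task of judging, before the statistical analysis, whether individual cases are excluded. For a list of situations it goes on: "the principal investigator shall comprehensively judge whether to exclude the subject based on the degree of completion of the test and the reasons for withdrawal", with explanations to be given. The list covers:

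- violation of the eligibility criteria;
- factors that the researcher considers incompatible with continuing, where the researcher has in fact discontinued the subject;
- poor compliance: "During the test, the subjects do not comply with the test plan and the compliance is poor", with uncollected efficacy and safety samples and absent data as examples, closed by an open-ended etc.

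Only the first ground can rest wholly on facts that existed before randomisation. No ground has a numerical threshold.

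**The concern.** Randomisation protects the comparison only if membership of the analysed groups does not depend on what happens afterwards. Here it may depend on compliance, on the investigator's own decision to discontinue a patient, and on completeness of data. People who are not said to be blinded weigh these after the data are in. Each ground can be related to prognosis.

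Two features add to this. Two possible reasons for removal, not taking the drug and not tolerating it, exist only in the voriconazole arm, so exclusions may differ between arms. The trial also expects very few events, so one or two decisions about recurrent patients can settle the result. If exclusion is related to recurrence, both the estimated effect and the type I error rate of the primary comparison are affected.

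**Working it through.** **Inputs (Study design and setting).** On recurrence: "the recurrence rate of the experimental group is expected to be less than 1%, and that of the control group is about 20" per cent. Error rates: "value of 0.05 and the degree of certainty of 0.8". Size: "to be 37 people, with the amplification of 1.1 times, and 40 patients are planned to be included in each group". The documents give no figure for how many patients will be excluded or which ones, so every exclusion fraction below is an assumption.

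**1. The plan's own figure.** For two proportions with unpooled variance and two-sided alpha,

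n = (1.960 + 0.842)² × [0.20 × 0.80 + 0.01 × 0.99] / (0.20 - 0.01)² = 7.849 × 0.1699 / 0.0361 = 36.9, so 37 per group.

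This reproduces the stated 37. At 40 per group, the control arm is expected to have 40 × 0.20 = 8 recurrences.

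**2. Sensitivity to one or two exclusions.** The control arm is held at 8/40. P values are two-sided.

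| Voriconazole recurrences | Fisher's exact | Pooled z |
|---|---|---|
| 1/40 | 0.029 | 0.013 |
| 2/40 | 0.087 | 0.043 |
| 3/40 | 0.193 | 0.105 |
| 1/39 (one of two excluded) | 0.029 | 0.015 |
| 2/39 (one of three excluded) | 0.087 | 0.047 |
| 1/38 (two of three excluded) | 0.029 | 0.016 |

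Under Fisher's test, removing one of two voriconazole recurrences crosses 0.05 (0.087 to 0.029). Under the pooled z test, 2/40 is already below 0.05, and the crossing comes when one of three is removed (0.105 to 0.047). The point of crossing depends on the test. That a single patient can cause it does not.

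**3. False-positive rate with no true effect.** Assume 20% recurrence in both arms, 40 per arm and no control exclusions. Exclude 10% of event-free voriconazole patients and a fraction q of recurrent ones. On average that removes 32 × 0.10 = 3.2 event-free patients plus 8q recurrent ones: 2.4 at q = 0.3 and 4.0 at q = 0.5. The expected recurrence proportion among those kept is 0.20(1 - q) / [0.20(1 - q) + 0.80 × 0.90]:

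- q = 0.3: 0.14 / 0.86 = 16.3%
- q = 0.5: 0.10 / 0.82 = 12.2%

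The chance of p ≤ 0.05 in favour of voriconazole, by simulation and by exact enumeration, is:

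| Exclusion in the voriconazole arm | Pooled z | Fisher |
|---|---|---|
| None | about 2.5% | 1.4% |
| 10% regardless of outcome | about 2.5% | 1.7% |
| 10% of event-free, 30% of recurrent | about 5.8% | 4.1% |
| 10% of event-free, 50% of recurrent | about 13.4% | 9.7% |

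The second row is the control calculation. The rise comes entirely from exclusion related to outcome, not from exclusion as such.

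**The case against.** Several stronger readings are tempting and should be set aside.

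- *The principal investigator decides alone.* The text does not establish this. The opening sentence of the section names the sponsor and the statistical unit as well, and explanations are required. It is unclear whose judgement prevails. None of the three parties is said to be blinded.
- *Those judging know who recurred.* The non-blind design supports knowledge of the arm. Nothing states that recurrence status is known at that point, and nothing states that it is withheld.
- *The rule is one-sided and favours voriconazole.* The compliance ground refers to the trial plan as a whole, and its examples are uncollected samples. Table 1 schedules samples and a compliance evaluation without separating the arms. Controls can be excluded too, and may miss visits. Only drug non-compliance and drug intolerance are specific to one arm, so bias in the other direction is also possible.

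The figures can also be challenged. The Statistical analysis section names Cox regression, which is neither of the tests used above. At the planned rate below 1%, fewer than 40 × 0.01 = 0.4 voriconazole recurrences are expected, so having two or three to exclude is not the planning scenario. Both points stand, and the figures are illustrations only.

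Finally, analysis sets are commonly left to a SAP, and the exclusions might be meant only for a per-protocol set. That disposes of any complaint that no intention-to-treat set is named. It does not dispose of the rule that the article does state, which confines the exclusions to no particular set.

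**Conclusion.** The concern holds as a rule fixed badly, not as an omission. The protocol article allows discretionary exclusion of randomised patients on post-randomisation grounds in an open trial, with no threshold and no protection from knowledge of arm or outcome. The direction of bias is not determined by the text; a spurious voriconazole benefit is one possible result.

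With 8/40 control recurrences, a single excluded voriconazole recurrence can move the result across 0.05 (from two events under Fisher, from three under the pooled z test). With no true effect, outcome-related exclusion of the assumed extent raises the chance of a false benefit from 2.5% to about 6-13% (pooled z), or from 1.4% to about 4-10% (Fisher). This rests on assumed exclusion of 10% of event-free and 30-50% of recurrent voriconazole patients and of no controls. If exclusion is unrelated to outcome, there is no such rise. Because the rule decides who enters the primary comparison, it should be corrected before outcome data accumulate. Trial status reports only 8 patients enrolled.

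**What to change.** Replace the exclusion rule with three statements.

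1. The primary analysis includes every randomised patient in the assigned arm, whatever their compliance, discontinuation or completeness of data.
2. The elimination list defines only a secondary per-protocol set. Its rules are objective (for example, a stated compliance threshold and stated minimum data) and are applied by people blind to arm and to recurrence.
3. Removal from the primary set is allowed only for ineligibility on facts that predate randomisation, judged blind to arm and outcome.

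The cost is about one paragraph of protocol or SAP wording. The planned 40 per group does not change. The downside is that the estimated effect may be slightly smaller than in a per-protocol set.
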